### 2.4. Eligibility criteria

The study will include patients in physiological coma (score between 3 and 8 on the Glasgow Coma Scale) or induced coma (score between 5 and 6, slow response to stimuli and deep sedation, respectively), on the Ramsay scale, submitted to invasive mechanical ventilation, indication of nasoenteral tube under medical prescription, aged 18 years or older. It is noteworthy that patients who lost the nasoenteral tube due to inadvertent exit or obstruction will also be included.

Exclusion criteria were: patients with coagulopathy (abnormal prothrombin time, partial thromboplastin time and platelet disorders); nasal stenosis; upper respiratory tract anomalies; esophageal disorders (esophageal hiatus hernia, esophageal varices, esophageal or nasopharyngeal carcinoma); skull base fracture; teeth with mobility and history of difficult intubation. In order to verify such information, medical records were consulted before the procedure was performed.

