### 2.10. Randomization and masking

Thirty-nine patients will be randomly divided into 3 groups. Patients allocated in the control group (CG) will have the tube inserted in the conventional way, that is, the head is kept in the neutral position, while the tube is gently inserted through one of the nostrils, without any maneuver or instrument.

Patients selected for the first intervention group (GI1) will have their heads turned to the right lateral position. This way, the tube will be inserted through the selected nostril without any neck maneuver or instrument.

For patients selected for the second intervention group (GI2), a conventional adult laryngoscope will be orally inserted. The tracheal tube and tongue will be raised to provide the best view of the larynx area. Thus, after viewing the piriform sinus or the esophagus, the tube will be inserted into the patient nostril and advanced to the esophagus under direct visualization. The patient head will be held in the neutral position and the blade will be gently lifted to avoid excessive neck extension.

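### The exclusion list has no item on whether the head can be turned, although one of the three randomised arms is defined by turning it

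*Protocol article*

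**What the plan says.** Section 2.4 includes intubated adults who are "patients in physiological coma (score between 3 and 8 on the Glasgow Coma Scale) or induced coma" and have a prescribed nasoenteral tube. The cause of coma is not restricted.

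The exclusions open with "Exclusion criteria were: patients with coagulopathy (abnormal prothrombin time, partial thromboplastin time and platelet disorders); nasal stenosis; upper respiratory tract anomalies; esophageal disorders" and close with "skull base fracture; teeth with mobility and history of difficult intubation". The footnote to Figure 1 gives the same list. Neither version mentions the neck, the cervical spine or head rotation.

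Section 2.10 states that "Thirty-nine patients will be randomly divided into 3 groups". It sets no eligibility condition for any single arm. For GI1, "Patients selected for the first intervention group (GI1) will have their heads turned to the right lateral position". In the control group and in the laryngoscope group (GI2) the head stays neutral. For GI2 the text adds: "The patient head will be held in the neutral position and the blade will be gently lifted to avoid excessive neck extension".

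**The concern.** Randomising among three techniques presupposes that every patient could receive any of them at the moment of allocation. The eligibility list secures this for the laryngoscope arm through the items on mobile teeth and difficult intubation. It does nothing comparable for the head-rotation arm.

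Two things are at stake. The first is safety: a comatose patient whose head cannot be turned could be assigned to have it turned. The second is the comparison of GI1 with the conventional method. If staff decline to turn the head after allocation, the departure from the assigned technique can arise only in GI1, because the same patient would have met no such obstacle in either neutral-head arm.

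**Working it through.** The plan states no figure on this point, so the main check sets the eligibility list against what each arm requires.

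**Step 1: what each exclusion screens for.** The article gives no reasons for its exclusions; the middle column is my reading.

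| Exclusion (section 2.4, Figure 1) | Hazard it bears on | Arm |
|---|---|---|
| Coagulopathy | Bleeding on insertion | All |
| Nasal stenosis | Nasal route | All |
| Upper respiratory tract anomalies | Nasal route, airway | All |
| Esophageal disorders | Esophageal passage | All |
| Skull base fracture | Nasal route | All |
| Mobile teeth | Laryngoscopy | GI2 |
| Difficult intubation | Laryngoscopy | GI2 |

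Of seven categories, two relate specifically to the GI2 technique and none to the GI1 manoeuvre. The count is the same in both places, so the gap is not an artefact of text extraction.

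**Step 2: does any other section close the gap?**

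- Section 2.6 says a script will be followed for each technique. It is not shown, and a script applied to an assigned technique acts after allocation.
- Section 2.8, primary outcome, allows another method only when more than three attempts are needed.
- Section 2.8, secondary outcome, stops the procedure only for signs of respiratory distress.
- Section 2.10 says that in GI1 the tube is passed without a neck manoeuvre. This describes insertion once the head has been turned; it does not remove the rotation.
- Section 2.13 removes and replaces a participant who withdraws. It does not say whether a patient whose head could not be turned would be handled this way. If so, such patients would leave GI1 but remain in the other two arms.

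None of these is a check before allocation.

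**Step 3: how often could it happen?** The documents give no prevalence. Let p be the share of otherwise eligible patients whose head cannot be turned. With independent patients and n in GI1, the chance of at least one such patient in that arm is 1 − (1 − p)^n.

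For n, section 2.9 gives a total of 39 with 13 controls and 26 for each intervention group, which would sum to 13 + 26 + 26 = 65. Thirteen per arm is the reading that fits three groups and a total of 39, so I take n = 13.

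| Assumed p | 1 − (1 − p)^13 |
|---|---|
| 1% | 1 − 0.99^13 = 12% |
| 2% | 1 − 0.98^13 = 23% |
| 5% | 1 − 0.95^13 = 49% |
| 10% | 1 − 0.90^13 = 75% |

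One such patient would be 1/13 = 7.7% of the arm. The spread shows that the result is driven almost wholly by the assumed p.

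**The case against.** The strongest reply is that this is an omission in an article that condenses a fuller protocol, and that the technique scripts are a natural place for precautions. Part of this stands: the scripts are not shown, so one cannot say that nobody will look at the neck. But the article does not leave eligibility to another document. It prints a specific list twice and identically, and it spells out technique-related items rather than trusting them to judgement. A precaution in a script would also come after randomisation, where it produces deviations and does not prevent them.

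A reader might also infer more than the text supports, in three ways.

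- *That excluding skull base fracture shows trauma patients are expected.* That item is explained by the nasal route in every arm. A precautionary exclusion says nothing about case mix, and sections 2.2 and 2.3 give none.
- *That the GI2 wording on neck extension shows the authors saw a cervical hazard and overlooked it in GI1.* The sentence also requires a neutral head, so it can equally be read as keeping the technique as defined.
- *That the comparison of GI1 with control is biased.* No section says a nurse may decline, what the patient would then receive, or how the patient would be analysed. The pathway is conditional, and no size or direction follows.

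These objections limit the claim. They do not supply the missing condition.

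**Conclusion.** The concern holds as a mismatch between section 2.4 with Figure 1 and section 2.10. The stated criteria admit a patient who cannot receive one of the three techniques, and nothing visible prevents allocation to that technique. The consequence is a safety concern or, if staff decline, non-adherence that falls on GI1 alone.

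This rests on the printed text and on no numerical assumption. The range of about 12% to 75% for at least one such patient rests on an assumed prevalence of 1% to 10%, 13 patients in GI1 and independence between patients. It illustrates scale and is not an estimate for this ICU. It would be wrong to conclude from it that the event is likely, or that the trial's results will be distorted in a known direction.

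**What to change.** Reconcile section 2.4 and Figure 1 with section 2.10 by adding one eligibility condition: the patient must be able to receive each of the three techniques. It should be checked and recorded before allocation and applied equally to all three arms. The investigators should define the specific clinical conditions that fail it, including those of the neck; this review proposes none. If the full protocol already contains such a condition, the published list and the figure footnote should be corrected to match.

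The cost is one amendment, slightly slower recruitment and results that do not apply to the patients excluded. Section 2.1 says data collection is ongoing, so patients will have been enrolled under two eligibility definitions. The report should give the number enrolled in each arm before and after the change.

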### 2.5. Recruitment

The study flowchart is described in Figure 1. Patients will be recruited upon the need for nasoenteral tube insertion the ICU. At the opportunity, the eligibility criteria for participation in the research will be applied. Subsequently, as critical patients admitted to the ICU are unable to consent, consent will be obtained from legal guardians prior to the intervention. Each research participant will have to fill out the Free Informed Consent Form, with the reading and signature of the respective family member legally responsible for the patient.

**Figure 1. F1:**
[figure not shown]
Flowchart of inclusion, allocation, follow-up procedures and study endpoints. Natal/RN, 2021. *Patients with coagulopathy (abnormal prothrombin time, partial thromboplastin time and platelet disorders); nasal stenosis; upper respiratory tract anomalies; esophageal disorders (esophageal hiatus hernia, esophageal varices, esophageal or nasopharyngeal carcinoma); skull base fracture; teeth with mobility and history of difficult intubation.

### 2.6. Allocation

In this study, only data analysts will be blinded to the treatment group to which participants were randomized. However, resources will be used to minimize, as much as possible, biases in research results.

For this, there will be a collaborating researcher (P1), who will be responsible for the allocation and randomization of patients prior to data collection using computer-generated random numbers, to be carried out through the “Research Randomizer” website (https://www.randomizer.org), in addition to the application of the collection instrument, verification of the insertion time and annotation of the vital signs and application of the collection instrument, as well as the reading of the insertion X-ray, to be performed immediately after the insertion of the nasally placed small-bowel feeding tube. Three nurses (E1, E2, E3) will be in charge of applying any of the programmed techniques. It is noteworthy that nurses responsible for applying the techniques are from the service where the data collection will be carried out and work on the day and night shifts and will be unaware of topics to be evaluated. Although the nurses are aware of the method that will be used for the insertion of the tube, they will not be aware of the objectives of the study. This way, only the investigation team will know which technique was used in each patient, and patients will not know due to their clinical condition.

To minimize biases, it is noteworthy that, prior to the data collection stage, nurses were trained in relation to the techniques applied to familiarize with the procedure, as this fact can influence the success rate and the time required for insertion. To this end, a previously elaborated script will be strictly followed for each of the techniques, with nurses being trained in theory and laboratory practice. Materials and monitoring equipment used will also be standardized. The PHILIPS CM10 Efficia multiparameter will be used to monitor all patients and the nasally placed small-bowel feeding tube (EMBRAMED).

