### 2.8. Endpoint

#### 1.2.8. Primary outcome.

The success rate on the first attempt will be considered as the dependent variable. Insertion success will be defined as the successful passage of the tube on the first attempt and confirmed by radiography of the correct anatomical positioning of the tube distal tip, which will be performed immediately after the procedure. If the nasally placed small-bowel feeding tube is not successfully inserted, it will be considered a failure and recorded as an unsuccessful attempt. Subsequently, new attempts will be performed.

The number of attempts required for successful insertion will be recorded for each patient. It should be noted that if more than 3 attempts are required, the procedure will be declared unsuccessful and data will be used to count failures. In these cases, the researchers may use another method of free choice for nasally placed small-bowel feeding tube insertion.

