### 2.11. Data collection

A data collection printed form containing variables about patients will be used, namely: Identification (bed; name initials; age; sex; date of birth); Clinical data (cause of admission; estimated weight, height and body mass index); Level of consciousness or Ramsay scale data, including type of drug used and sedation duration; Endotracheal tube number and cuff pressure; Data regarding the technique used (technique; number of attempts; required time in seconds; complications, if any); Parameters to be evaluated (heart and respiratory rate, blood pressure and oxygen saturation) before, during and after nasally placed small-bowel feeding tube insertion using each of the techniques; Confirmation of the correct nasally placed small-bowel feeding tube positioning by chest and abdomen radiography in bed.

Table 1 shows the detailed study stages, with the Standard Protocol Items for Randomized Trials schedule of enrollment, interventions, and assessments.

**Table 1 T1:** Description of the study stages: P1: Day 1—request for nasally placed small-bowel feeding tube insertion in the patient and intervention. F1: evaluation after the procedure until X-ray is performed.

Study period					
			Post-allocation: Allocation, interventions, follow-up		
Timepoint	Enrollment	Baseline	Allocation	P1 intervention	Follow-up (F1)
Enrollment:					
Eligibility criteria	X				
Recruitment	X				
Initial assessment	X				
Informed consent	X				
Allocation			X		
Interventions:					
Insertion in a conventional manner (control group)				⟷	X
Insertion with the head turned to the right side (intervention group)				⟷	X
Insertion with laryngoscope (intervention group)				⟷	X
Assessments:					
Identification, clinical data, level of consciousness, SSVV, among others		X			

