### 2.12. Data collection and management

The principal researcher will be responsible for recruiting participants and applying the data collection instrument. Three nurses will be responsible for applying the intervention in the control and intervention groups, without knowing what will be evaluated.

The participation of patients will be carried out on a voluntary, nonprofit basis and will occur upon reading and signing the Free and Informed Consent Form by the family member, which demonstrates that the individual accepts to participate in the research, explaining all stages, objectives, risks and benefits of the research. It is possible for participants to dropout at any stage of the research without prejudice to treatment and without suffering penalties or judgments of any kind.

The researchers will ensure that the anonymity of participants is protected and their data will remain confidential so that their identities and any type of identity information is protected. Two copies of the consent form will be provided, both signed by a family member and responsible researchers.

The results of this research will be presented at meetings or publications; however, the identity of participants will not be revealed. Original documents and files will be kept at the test sites for 15 years. The principal investigator is responsible for storing data and files and will have access to the final set of data and dissemination.

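### The unblinded researcher who allocates the arm and times the insertion also reads the X-ray that confirms first-attempt success, and no named researcher is unaware of the arm

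*Protocol article*

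**What the plan says.** Section 2.6 (Allocation) states that "only data analysts will be blinded to the treatment group to which participants were randomized". It then lists the tasks of P1, a collaborating researcher: randomization and allocation, the collection form, the insertion time, the vital signs, "as well as the reading of the insertion X-ray, to be performed immediately after the insertion". It adds that "only the investigation team will know which technique was used in each patient", and it sets the aim that "resources will be used to minimize, as much as possible, biases in research results".

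The primary outcome part of 2.8 requires that the tube pass on the first attempt and that this be "confirmed by radiography of the correct anatomical positioning of the tube distal tip". The film is therefore a necessary part of the primary endpoint. Under the secondary outcomes, bending, twisting, knotting and tracheal insertion are also looked for on X-ray.

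Section 2.11 describes one printed form that holds both the arm ("Data regarding the technique used (technique; number of attempts; required time in seconds; complications, if any") and the confirmation of correct tube "positioning by chest and abdomen radiography in bed".

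Section 2.12 gives the same form to someone else: "The principal researcher will be responsible for recruiting participants and applying the data collection instrument".

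**The concern.** P1 assigns the technique and is at the bedside to time it. P1 then decides from the film whether the tip is where it should be. Reading errors that are unrelated to the arm mostly add noise. Errors that lean by arm go straight into the difference in first-attempt success, which is the trial's main comparison. Blinding the analysts comes too late, because the score they receive has already been made by someone who knows the arm. The nurses' unawareness of the study aims does not help either, because they do not read the film.

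Some judgement enters the reading. The article asks for correct anatomical position without saying which position counts, while 2.7 measures the tube length to reach the jejunum. The full protocol may define it.

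With 13 patients per arm, one film is worth 1/13 = 7.7 points. The abstract lists unblinded nurses as a limitation, which is unavoidable here. It does not mention the unblinded film reader, which is avoidable.

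**Working it through.** **Step 1. Who knows the arm when the film is read?** This is settled by setting the sections side by side.

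| Role | Duties stated | Aware of the arm? |
|---|---|---|
| P1 (2.6) | Allocates, times, fills in the form, reads the film | Yes |
| Nurses (2.6, 2.12) | Carry out the technique | Yes, but they do not read the film |
| Principal researcher (2.12) | Recruits, applies the form | Yes: the form records the technique (2.11), and 2.6 says the investigation team knows it |
| Data analysts (2.6) | Analyse | Blinded, but no film reading is stated |

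So the film is read with the arm known, and no other named researcher is free of that knowledge as the duties now stand. Sections 2.6 and 2.12 also assign the same form to two different roles.

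**Step 2. How large could the effect be?** The plan gives no figure for misreading, so this is a range under assumptions.

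Inputs:
- n = 13 per arm, from 39 patients in 3 groups (2.10). Section 2.9 says 26 in each intervention group, which does not sum to 39; it is read here as 26 in both together.
- True first-attempt success p, the same in both arms. The only rate in the document is 86/104 = 82.7%, from an outside study described in the Introduction. Lower values down to 50% are added as assumptions.
- u = share of true first-attempt failures in one intervention arm read as success. Assumed 10% to 30%.

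The observed rate in that arm is p + u(1 − p), so the overstatement is u(1 − p). The chance of a significant result is the exact binomial sum over all tables of 13 v 13 with two-sided Fisher p < 0.05.

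| p | Overstatement, u = 0.1 to 0.3 | Patients of 13 | Fisher rejection, u = 0 | Fisher rejection, u = 0.1 to 0.3 |
|---|---|---|---|---|
| 82.7% | 1.7 to 5.2 points | 0.2 to 0.7 | 1.2% | 1.1% to 1.3% |
| 80% | 2.0 to 6.0 points | 0.3 to 0.8 | 1.4% | 1.4% to 1.8% |
| 50% | 5.0 to 15.0 points | 0.65 to 1.95 | 2.9% | 3.4% to 7.7% |

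Example: at 82.7%, 0.3 × (1 − 0.827) = 0.052. At 50%, 0.3 × 0.5 = 0.15.

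**Step 3. What if most failures never depend on the film?** In the study described in the Introduction, 130 attempts in 104 patients leave 26 failed attempts, matching the 23 oral and 3 tracheal deviations. Assume that oral deviations are recognised without a film; the protocol does not say so. Then about 3/26 of failures are open to misreading. The overstatement becomes (3/26) × u × (1 − p): 0.2 to 0.6 points at 82.7%, and at most (3/26) × 0.3 × 0.5 = 1.7 points at 50%.

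**Step 4. What can a single film do?** As an illustration against 8/13, moving the other arm from 12/13 to 13/13 changes the two-sided Fisher p from 0.160 to 0.039.

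**The case against.** The strongest reply is that the effect is probably small. Tip position on a film is fairly objective, and the film is only one half of the success definition. A tube coiled in the mouth or lying in the trachea is a gross error, not a borderline call. At 82.7% success the Fisher rejection rate hardly moves, and the 15-point shift and 7.7% rejection rate belong only to the corner with 50% success and 30% misreading. All of this stands, and it limits the weight of the point. It does not remove it: the assignment of the reading is stated text, not a detail left to a fuller document, and it falls short of the aim in 2.6 to keep bias as low as possible. The 82.7% comes from one outside study and need not hold in this trial.

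A reader might infer that the principal researcher in 2.12 is already a second assessor who could score the film without the arm. The documents do not support that. That role applies the form on which the technique is written, and 2.6 says that the investigation team knows the technique. It becomes possible only after duties are changed. P1 and the principal researcher may even be one person.

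It is also fair to say that a blinded film score is a partial remedy. Attempts given up before a film, the number of attempts and the summed time would still rest on unblinded bedside judgement.

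**Conclusion.** The point holds. The article fixes P1 as film reader and fixes that only analysts are blinded, so the radiographic part of the primary endpoint is scored with the arm known. Under the stated assumptions (13 per arm, equal true success, 10% to 30% of failures misread in one arm only) the overstatement is 1.7 to 5.2 points at 82.7% success and up to 15 points at 50%. It is below 1 point at 82.7% if oral deviations are spotted without a film, and nil if the reading does not lean by arm. The harm is mainly to the estimated difference and less to the test.

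A reader might go further and infer that the primary result will be biased or the false-positive rate inflated. The documents show an avoidable risk, not that P1's reading would lean. This should be fixed, with medium confidence in its practical importance.

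**What to change.** 1. Let P1 alone apply the form, as 2.6 says, and change 2.12 to match. P1 withholds completed forms until the film scores are locked.
2. Let the principal researcher, whose remaining duty of recruitment comes before allocation, score the existing first-attempt film by study number. The arm is withheld and any view of head position is masked. State in 2.8 that this score supplies the radiographic confirmation in the primary endpoint, and that P1's immediate reading only guides care.
3. If the two roles are one person, score the stored films in a coded, shuffled batch without the form, and report that blinding was incomplete.
4. Where the blinded score and P1's reading differ, the blinded score decides the confirmation. The number of attempts and the summed time stay as performed. Report disagreements by arm.
5. Data collection is ongoing (2.1). Rescore earlier films in the same way, by someone who has not seen that patient's arm. Where that is not possible, keep P1's reading and mark it.

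Cost: at most 39 extra film readings by existing staff, with no new X-ray, and wording changes in 2.6, 2.8 and 2.12. It relies on the films being retrievable, which the article does not state. Some records will disagree, for example a second attempt made after a first that is later scored as correct. Failures judged at the bedside, attempt count and time remain unblinded.
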